## Abstract

**Background:**

Pre-eclampsia (PE) is related to an impaired endothelial function. Endothelial dysfunction accounts for altered vascular reactivity, activation of the coagulation cascade and loss of vascular integrity. Impaired endothelial function originates from production of inflammatory and cytotoxic factors by the ischemic placenta and results in systemic oxidative stress (OS) and an altered bioavailability of nitric oxide (•NO). The free radical •NO, is an endogenous endothelium-derived relaxing factor influencing endothelial function. In placental circulation, endothelial release of •NO dilates the fetal placental vascular bed, ensuring feto-maternal exchange. The Endopreg study was designed to evaluate in vivo endothelial function and to quantify in vitro OS in normal and pre-eclamptic pregnancies.

**Methods/design:**

The study is divided into two arms, a prospective longitudinal study and a matched case control study. In the longitudinal study, pregnant patients ≥18 years old with a singleton pregnancy will be followed throughout pregnancy and until 6 months post-partum. In the case control study, cases with PE will be compared to matched normotensive pregnant women. Maternal blood concentration of superoxide (O_2_•) and placental concentration of •NO will be determined using EPR (electron paramagnetic resonance). Endothelial function and arterial stiffness will be evaluated using respectively Peripheral Arterial Tonometry (PAT), Flow-Mediated Dilatation (FMD) and applanation tonometry. Placental expression of eNOS (endothelial NOS) will be determined using immune-histochemical staining. Target recruitment will be 110 patients for the longitudinal study and 90 patients in the case-control study.

**Discussion:**

The results of Endopreg will provide longitudinal information on in vivo endothelial function and in vitro OS during normal pregnancy and PE. Adoption of these vascular tests in clinical practice potentially predicts patients at risk to develop cardiovascular events later in life after PE pregnancies. •NO, O_2_•^−^ and eNOS measurements provide further inside in the pathophysiology of PE.

**Trial registration:**

This trial has been registered on clinicaltrials.gov. ClinicalTrials.gov Identifier: NCT02603913. Registered October 2015.

## Background

Pre-eclampsia (PE) is a potentially life-threatening pregnancy related vasculopathy characterized by hypertension and proteinuria. PE results in high morbi-mortality for both mother and her unborn child. Between five and 10 % of pregnancies are complicated by hypertensive disorders and worldwide the incidence of PE has increased by 25% in the past two decades [1].

In normal pregnancy vascular remodelling of the maternal uterine spiral arteries occurs. Trophoblast cells invade the spiral arterioles within the first 12 weeks of pregnancy and replace the muscular wall of the vessels converting them into wide bore, low resistance, large capacity vessels, a process normally completed by 20 weeks gestation [2]. The free radical nitric oxide (•NO) is an important mediator of the placentation process. •NO is an endogenous endothelium-derived relaxing factor influencing endothelial function. Under physiologic conditions, endothelial release of •NO in the placental circulation dilates the fetal placental vascular bed, ensuring feto-maternal exchange [3]. •NO is formed out of L-Arginine by NOS (Nitric Oxide Synthase). This reaction is regulated by VEGF (Vascular endothelial growth factor), an endothelial mitogen that has an important function in the proliferation of endothelial cells and in angiogenesis. VEGF stimulates eNOS (endothelial NOS) and induces therefore •NO production [4]. In an oxidative environment, the lack of NOS-stabilizing factors results in NOS-uncoupling. NOS-coupling causes a shift from •NO production to superoxide (O_2_•^−^) production which maintains an oxidative setting.

The pathogenesis of generalized endothelial dysfunction is well known in PE and is subdivided into two phases. The first phase exists of a poor trophoblast invasion of the spiral arteries during the placentation process, causing failure to transform the placental bed arteries from high to low resistance vessels. This results in local ischemia, reperfusion damage and oxidative stress (OS). The local damage activates the second phase where disturbed production of angiogenic and anti-angiogenic factors (placental growth factor (PlGF) and soluble fms-like tyrosine kinase 1 (sFlt-1), respectively) results in systemic inflammation, endothelial activation, systemic OS and altered endothelial •NO production [5, 6]. When this vascular endothelial activation and dysfunction occurs at the level of liver, kidney, brain and placenta, the clinical presentation of PE arises [7].

In the past, PE has been divided in two different entities; angiogenic or placental PE (formerly called early onset, before 34 weeks) and non-angiogenic or maternal PE (formerly called late onset, after 34 weeks) [8]. Impaired placentation and endothelial dysfunction have been described in placental PE, whereas pre-existing maternal cardiovascular risk factors (essential hypertension, high BMI, diabetes, renal disease,..) usually precede maternal PE. This description however oversimplifies and overstates recent existing findings. Maternal risk factors can precede early onset PE as well as abnormal concentrations of placental angiogenic factors are found in late onset PE [6]. Fetal growth restriction and endothelial dysfunction caused by systemic inflammation are usually described in placental PE, nevertheless they are common in late onset PE. It is therefore more accurate to state that both maternal and placental factors contribute to PE and research should focus on classifications based on pathophysiologic processes, for instance endothelial and vascular dysfunction and amount of systemic inflammation and OS [9, 10].

In normal pregnancy, placental OS is present during all three trimesters and is necessary to obtain normal cell function, including activation of redox-sensitive transcription factors and activation of protein kinases [11–15]. Although OS is a common necessary feature of normal pregnancy, persistent OS gives rise to different disease-states, such as PE [13, 15–17]. Although considerable research has been devoted to OS in PE [13–15], less attention has been paid to the evolution of OS during the course of normal pregnancy. Little research has described an increase in •NO concentration with gestational age, suggesting an important role for •NO in the cardiovascular changes of normal pregnancy [3].

Recent literature has elucidated that PE is an important risk factor for cardiovascular disease in later life. Bellamy et al. and McDonald et al. describe a 3-fold risk for hypertension and a 2-fold risk of ischemic heart disease and stroke in women with a history of PE [18–21]. Women with hypertensive disorders during pregnancy also have a greater risk of chronic kidney disease and end-stage renal disease [22, 23]. With a view to detecting those women at risk, objectifying endothelial function and vascular function after healthy pregnancy and PE can help to establish reference values for disturbed post-pregnancy vascular function.

## Methods/design

### Study hypothesis

Endothelial and vascular function improve during healthy pregnancy to answer the higher hemodynamic demands. Due to the deficient placentation in PE, disturbed production of (anti-) angiogenic and inflammatory factors results in arterial stiffness and endothelial dysfunction. After PE, this vascular dysfunction continues in patients at risk for developing cardiovascular events later in life.

A certain amount of OS is necessary in healthy pregnancy. The deficient placental oxygenation in PE causes excessive local formation of reactive oxygen and nitrogen species (O_2_•^−^ and •NO respectively). When the balance between pro-oxidant species and the antioxidants is disturbed, OS arises. We hypothesize that in PE, there is a higher amount of O_2_•^−^ in the maternal circulation and a lower concentration of •NO and eNOS measurable in the placenta.

Endothelial and vascular dysfunction is correlated to the amount of OS present in the circulation.

### Objectives

#### Primary study objective

To evaluate OS during pregnancy.

Measurement of •NO in placental tissue and O_2_•^−^ in maternal blood using EPR.

Measurement of eNOS in placental tissue using immuno-histochemical staining.

*Prospective longitudinal study*: To evaluate the OS profile in normal pregnancies.

*Matched case-control study:* To compare the OS profile in normal versus PE pregnancies.

#### Secondary study objectives

To evaluate endothelial function during pregnancy (using peripheral arterial tonometry (PAT) and flow mediated dilatation (FMD) techniques) and to relate endothelial function to •NO, O_2_•^−^ and eNOS concentration.

*Prospective longitudinal study:* To evaluate endothelial function in normal pregnancies.

*Matched case-control study:* To compare endothelial function in normal versus complicated pregnancies.

To evaluate arterial stiffness during pregnancy (Pulse wave velocity, pulse wave analysis using Sphygmocor ®) and to relate arterial stiffness to •NO, O_2_•^−^ and eNOS concentration.

*Prospective longitudinal study:* To evaluate arterial stiffness in normal pregnancies.

*Matched case-control study:* To compare arterial stiffness in normal versus complicated pregnancies.

### Methodology

#### Study design

##### Single centre prospective longitudinal study

The first part of the study will have a prospective longitudinal design. Pregnant women in their first trimester of pregnancy will be eligible and will be followed throughout pregnancy and until 6 months postpartum.

##### Multicentre matched case-control study

The second part is a case control study where patients with pregnancies complicated by PE will be compared to normotensive controls, matched for maternal and gestational age, parity, smoking behaviour, BMI and ethnic group. Patients will be followed throughout (the rest of their) pregnancy and until 6 months postpartum. Matching will reduce the risk of bias.

#### Study population

##### Inclusion criteria

Prospective longitudinal study
Pregnant women ≥18 years old with a singleton pregnancy
2.Matched case-control study
Pregnant women ≥18 years old with a singleton pregnancy and > 20 weeks of pregnancyCases:
Pre-eclampsia following the revised ISSHP definition (2014) is [24]:

Hypertension (> 140 mmHg systolic or > 90 mmHg diastolic) developing after 20 weeks gestation and the coexistence of one or more of the following new onset conditions:
Proteinuria (spot urine protein/creatinine > 30 mg/mmol [0.3 mg/mg] or > 300 mg/day or at least 1 g/L [‘2 +’] on dipstick testing)Other maternal organ dysfunctionrenal insufficiency (creatinine > 90 μmol/L)liver involvement (elevated transaminases – at least twice upper limit of normal - and/or severe right upper quadrant or epigastric pain)neurological complications (examples include eclampsia, altered mental status, blindness, stroke, or more commonly hyperreflexia when accompanied by clonus, severe headaches when accompanied by hyperreflexia, persistent visual scotomata)hematological complications (thrombocytopenia: platelet count below 150,000/dL, DIC, hemolysis)Uteroplacental dysfunction: fetal growth restriction
◦ Hypertension greater than or equal to 140 mmHg systolic or 90 mmHg diastolic, must be confirmed at least 4 h apart. Hypertension greater than or equal to 160 mmHg systolic or 110 mmHg diastolic can be confirmed after a short interval (minutes) to facilitate antihypertensive treatment [25].

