##### Markers of systemic inflammation

Performing a complete blood count (CBC), the neutrophil/lymphocyte ratio (NLR), mean platelet volume (MPV) and platelet count will be obtained using a ADVIA 120 Hematology System (Siemens healthcare, Germany) [31–33].

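### The platelet threshold in the pre-eclampsia case definition is printed with an impossible unit: 150,000 per dL is 1.5 per μL

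*Protocol article*

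**What the plan says.** The Inclusion criteria for the matched case-control study introduce the case definition with "Pre-eclampsia following the revised ISSHP definition (2014) is" and a literature citation, then print the definition in full. A case needs hypertension arising after 20 weeks and "the coexistence of one or more of the following new onset conditions". The list covers proteinuria, renal, liver, neurological and haematological features, and fetal growth restriction. The haematological entry names thrombocytopenia, specified as "platelet count below 150,000/dL", and beside it "DIC, hemolysis".

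Platelet count appears in two other places. The section Markers of systemic inflammation says that "mean platelet volume (MPV) and platelet count will be obtained using a ADVIA 120 Hematology System", and the legend of Fig. 1 lists platelet count among the laboratory parameters. Neither gives a unit or a cut-off.

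The section Multicentre matched case-control study says that the comparison group consists of normotensive women.

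**The concern.** The figure is a decision threshold inside an inclusion criterion, not background text. It stands among other cut-offs that carry their own units, such as those for proteinuria and creatinine, so a reader would expect to be able to apply it as printed. A count of 150,000 in a whole decilitre of blood is so low that no patient could fall below it.

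What is at stake is the classification of one kind of patient. Consider a woman with new hypertension after 20 weeks whose only additional feature is a low platelet count. Under the printed number she is not a case. She cannot serve as a control either, because she is not normotensive. Anyone who codes the case definition from the printed text, or tries to replicate it, would leave her out of both groups.

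**Working it through.** **Inputs**

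- Printed threshold: 150,000 per dL (Inclusion criteria).
- Conversion: 1 dL = 100 mL = 100,000 μL, and 1 L = 10 dL (standard units, not from the article).
- Group size: 44 per group, from a difference of 0.3 in RHI, a standard deviation of 0.5, two-sided α = 0.05 and 80% power (Sample size calculations).

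**Step 1: convert the threshold**

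- Per μL: 150,000 / 100,000 = 1.5 per μL.
- Per litre: 150,000 × 10 = 1,500,000 per L = 0.0015 × 10^9/L.

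**Step 2: can any count fall below it?**

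The article gives no platelet counts, so the counts below are assumptions that span a wide range. Each is divided by the printed threshold of 1.5 per μL.

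| Assumed count per μL | Same count per dL | Multiple of the printed threshold |
|---|---|---|
| 100,000 | 10,000,000,000 | about 66,667 |
| 10,000 | 1,000,000,000 | about 6,667 |
| 1,000 | 100,000,000 | about 667 |

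The conclusion does not depend on which count is chosen. For scale only, the same numeral read per μL would be 150,000 × 100,000 = 15,000,000,000 per dL, which is 100,000 times the printed threshold.

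**Step 3: could this be a fault of text extraction?**

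That is unlikely. The micro sign is intact in the creatinine criterion of the same section, and again in the sections on placental •NO and maternal O2•−, where volumes are in μl. The unit dL is a complete and different unit, not one with a character lost.

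**Step 4: does another part of the article supply the unit?**

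No. The two other mentions of platelet count carry neither unit nor threshold.

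**Step 5: which women are affected?**

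One listed condition is enough for case status. Proteinuria, renal, liver and neurological features, DIC, hemolysis and fetal growth restriction do not depend on the platelet figure. Only women whose sole qualifying condition is a low platelet count are touched. The article gives no basis for putting a number on them.

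**Step 6: does it reach the sample size or the analysis?**

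The usual two-means formula gives n per group = 2 × (1.960 + 0.842)² × 0.5² / 0.3² = 2 × 7.85 × 0.25 / 0.09 = 43.6, which rounds up to 44. This reproduces the article's figure, and no platelet value enters it. The planned comparisons by t test or Mann-Whitney U test do not use the threshold either.

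**The case against.** The strongest reply is that nobody would apply this number. The entry names thrombocytopenia in words, and the section cites a published definition that an investigator can consult. A threshold of 1.5 platelets per μL is so implausible that it shows itself to be a slip. The dangerous threshold error is one that looks reasonable and gets used, and this one does not look reasonable. If sites use the unit that was evidently meant, the effect on recruitment is nil. Cases are also to be recruited up to 45, so leaving out a few women would not in itself reduce power.

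Most of this stands, and it limits how far the point can be taken. A reader might infer that thrombocytopenia can never qualify a woman for this study. The article does not support that as a statement about conduct: the condition is named, the source definition is cited, and the impossibility belongs only to the printed number. A reader might also infer that centres will correct the slip in different ways and so apply different rules. Nothing in the article points to that, and it offers no second plausible reading of the numeral. Nor does it support any estimate of how many cases would be lost. Finally, a journal article condenses a fuller protocol, and whether that document carries the same slip cannot be seen here.

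The reply does not make the printed figure right. The article sets out the criterion in full with its own number and unit, that number is wrong, and no other part of the article corrects it.

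**Conclusion.** The platelet threshold is wrong as written, and the matter is minor. As printed it equals 1.5 per μL and cannot be met. Under a literal reading, a hypertensive woman whose only other feature is a low platelet count falls outside both groups. The conversion is exact. That realistic counts lie far above 1.5 per μL is general knowledge rather than a figure from the article, but the margin is so wide that the result does not turn on it.

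The consequence is confined to that one subgroup, and it arises only if the printed number is actually applied. Since this is very probably a unit misprint, the practical effect may be none. The documents show no bias in any planned comparison and no loss of power.

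**What to change.** Check the platelet entry in the Inclusion criteria against the definition that the protocol cites, and correct the printed unit so that the two agree. The sponsor should take the value from that source; none is proposed here. If the full protocol carries the same text, correct it there too.

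The cost is a one-word correction to the eligibility text. Sample size, assessments and analysis stay as they are.

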##### Exclusion criteria

Exclusion criteria are (gestational) diabetes, multiple pregnancies, fetal abnormalities, hypercholesterolemia, renal disease, auto-immune disorders and connective tissue disease. Intake of low-dose aspirin or vitamin C supplements (> 500 mg/day) is an exclusion criterion. Since in Belgium folic acid is an advised pre- and periconceptional therapy, this will not act as an exclusion criterion.

The use of other medication/supplements will be listed in the patients record to find eventual confounders afterwards.

#### Description of investigations (scheme of investigations, Fig. 1)

##### Endothelial function (FMD)

The gold standard for non-invasive assessment of endothelial function is FMD, measuring NO-dependent vasodilation of the brachial artery in response to reactive hyperaemia [26]. An ultrasound diagnostic instrument (Prosound alfa6, Hitachi Aloka Medical ®) equipped with vascular software for 2D-imaging, colour Doppler imaging and ECG-triggering, are used with a high frequency linear array transducer (UST-5413, 5-13 MHz, Hitachi Aloka Medical ®). Patients are in a resting, supine position with the arm in a comfortable position for imaging the brachial artery. A blood pressure cuff is placed on the forearm with the upper border of the cuff at a distance of 5 to 10 cm distal from the elbow (lateral epicondyle). The brachial artery is imaged above the antecubital fossa in a longitudinal plane with a clear delineation of both anterior and posterior intima-media interfaces. A special probe-holding device is used to ensure consistency of images during the measurement. The baseline artery diameter is automatically tracked and the waveform of diameter changes over the cardiac cycle is displayed in real time using an automated edge detection system. (eTracking system, Aloka ®). Arterial occlusion is created by cuff inflation to supra-systolic pressure at least 50 mmHg above systolic pressure (minimum value of 200 mmHg) for 5 min. Low–flow-mediated constriction (LFMC) is calculated as the percent decrease in arterial diameter in the last 30 s of cuff occlusion as compared with resting diameter [27]. After 5 min of occlusion, the cuff is deflated. Brachial diameter is recorded continuously (eTracking) from the time point of cuff inflation to 5 min after cuff deflation. FMD (in % from baseline value) is expressed as (post-ischemic maximal diastolic diameter change - baseline diastolic diameter)/baseline diastolic diameter [26]. During the measurements, brachial artery blood flows will be measured at 3 different time-points; at rest, 15 s before cuff deflation, and immediately upon cuff deflation using pulsed-wave Doppler [27]. All recordings are performed by two experienced investigators ([name]).

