### Statistical methods

#### Sample size calculations

As sample size determining factor, we took the RHI since this is an important variable in our study, there is normal distribution and the population standard deviation is known.

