#### Descriptive statistics and data analysis

##### Prospective longitudinal study

For the physiologic study of the RHI in pregnancy we will calculate the reference values and 95% confidence interval. Longitudinal data will be plotted and a linear mixed-effects model with random intercept will be fitted. Percentiles for RHI, FMD and PWV/PWA will be calculated based on this model. Correlation coefficients between baseline RHI, FMD PWV/PWA, UA Doppler PI, fetal biometry, NLR, MPV, MAP, birth-weight percentile, eNOS, •NO and O_2_•^−^ will be analysed.

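### The printed FMD formula subtracts the baseline diameter from a quantity that is already a change, so read literally it gives FMD minus 100 percentage points

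*Protocol article*

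**What the plan says.** All the defining text is in the protocol article, under Description of investigations, Endothelial function (FMD).

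- The purpose of the test is given as "measuring NO-dependent vasodilation of the brachial artery in response to reactive hyperaemia".
- The raw data are diameters: "Brachial diameter is recorded continuously (eTracking) from the time point of cuff inflation to 5 min after cuff deflation".
- The unit and the formula share one sentence. It begins "FMD (in % from baseline value) is expressed as" and continues, after an opening bracket, "post-ischemic maximal diastolic diameter change - baseline diastolic diameter)/baseline diastolic diameter".
- The companion measure, low-flow-mediated constriction, is "calculated as the percent decrease in arterial diameter in the last 30 s of cuff occlusion as compared with resting diameter".

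FMD is used in both parts of the study. For the longitudinal part, the analysis section fits a linear mixed-effects model with a random intercept and says "Percentiles for RHI, FMD and PWV/PWA will be calculated based on this model". It also lists FMD among the variables to be correlated. For the case-control part, FMD is among the continuous variables to be summarised (mean, standard deviation and 95% confidence interval, or median and interquartile range) and compared by t test or Mann-Whitney test. FMD belongs to the secondary objectives. No other section gives a different FMD formula.

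**The concern.** Percentage dilatation is the rise in diameter divided by the baseline diameter. It can be written as (peak − baseline)/baseline or as change/baseline. The printed line mixes the two: it starts from the change and then subtracts the baseline as well. The result is negative for any dilatation below 100%, so it cannot be the vasodilation the section sets out to measure.

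What is at stake is the level of the reported values. Reference percentiles, group means and medians are all read on an absolute scale. The article's Discussion also sets the study against earlier FMD findings in pregnancy. An analyst who derived FMD from exported diameters by the printed rule would report values on a scale shifted by 100 points.

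**Working it through.** **Inputs.** The formula and its unit come from the FMD section. The documents state no FMD value, no brachial diameter and no FMD-based design figure, so there is no published number to reproduce. All FMD values and diameters below are assumptions for illustration.

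**Algebra.** Let D0 be the baseline diastolic diameter, D1 the maximal post-ischaemic diastolic diameter, and Δ = D1 − D0 the change.

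- Intended: FMD = (D1 − D0)/D0 = Δ/D0.
- As printed: (Δ − D0)/D0 = Δ/D0 − 1 = FMD − 1.

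In percentage units the printed result is FMD − 100. D0 cancels from the offset, so the offset is the same for every woman and every visit.

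**Worked example (assumed D0 = 3.5 mm, assumed true FMD = 10%).** D1 = 3.5 × 1.10 = 3.85 mm and Δ = 0.35 mm.

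- Intended: 0.35/3.5 = 10%.
- As printed: (0.35 − 3.5)/3.5 = −3.15/3.5 = −90%.

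**Range.** The results are the same at assumed baselines of 3.0, 3.5 and 4.0 mm:

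| Assumed true FMD | Formula as printed | After correction |
|---|---|---|
| 2% | −98% | 2% |
| 5% | −95% | 5% |
| 10% | −90% | 10% |
| 15% | −85% | 15% |
| 20% | −80% | 20% |

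**What a constant shift changes.** Write Y* = Y − 100 for every observation.

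- Mean, median, quartiles, and the limits of a confidence interval for a group mean: each falls by 100.
- Mixed model: the intercept falls by 100, while slopes and variance components stay the same. Percentiles derived from the model therefore fall by 100.
- Difference between groups: (Y1 − 100) − (Y2 − 100) = Y1 − Y2, unchanged, and so is its confidence interval.
- Standard deviation, t statistic, ranks (hence the Mann-Whitney test) and correlation coefficients: unchanged.

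**Sample size.** The sample size section says "As sample size determining factor, we took the RHI". With a difference of 0.3, a standard deviation of 0.5, 80% power and two-sided α = 0.05, the usual two-group calculation gives 44 per group, which matches the article. FMD does not enter it.

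**The case against.** The best reply is that this is a one-word slip that its own sentence exposes. Once *change* is dropped, or the phrase is read loosely as the diameter reached at maximal change, the expression is the ordinary percentage change. The neighbouring constriction measure is worded correctly, the unit is stated, and a result near −90% would be noticed at once. The recordings use automated edge detection and are made by two experienced investigators, and nothing shows that anyone will compute FMD by the literal text.

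Most of this stands. The slip is the likeliest explanation, and misuse is not shown. But the documents do not say whether the software or an analyst derives FMD, so the tracking system cannot be assumed to guard against the error. The line is the article's only FMD formula, and it sits in the methods as an outcome definition. That readers can guess the intention does not make the printed rule correct.

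A reader might go further and infer that the comparison of FMD between pre-eclampsia and controls is compromised, or that the study's FMD reference values will be wrong. The documents support neither. The shift cancels in every between-group comparison and is fully reversed by adding 100. The percentiles are planned, and they would be wrong only if the formula were followed to the letter.

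**Conclusion.** The formula is wrong as written. Read literally, it equals true FMD minus 100 percentage points, which contradicts the stated unit. This conclusion is algebraic and needs no assumption about diameters. Only the illustrative results of −98% to −80% do, and they rest on an assumed true FMD of 2% to 20%.

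The consequence is conditional and narrow. If the text is followed literally, reported FMD levels, interval limits for those levels and model-based percentiles are all displaced by 100 points. Tests, group differences, correlations, mixed-model slopes and the RHI-based sample size are untouched. With FMD a secondary measure and the cause most likely a drafting slip, this is a minor correction to an outcome definition and no threat to the study's inferences.

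**What to change.** Delete *change* from the numerator, so that the definition reads:

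FMD (%) = 100 × (post-ischaemic maximal diastolic diameter − baseline diastolic diameter) / baseline diastolic diameter.

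Writing 100 × (maximal diastolic diameter change)/(baseline diastolic diameter) is equivalent, but only one form should appear. Then confirm that whatever produces the FMD variable, the eTracking export or an analyst's derivation, uses this definition.

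The cost is one line of text and one check of the derivation. No change to the design, sample size or planned analyses follows.
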